### Allocation and implementation of interventions

Prior to the endovascular intervention, patients will be enrolled, and informed consent will be obtained from all participants by surgeons. The included patients were randomly allocated at a 1:1 ratio to the CBE stenting group or the CSE stenting group using Statistical Analysis System (SAS, version 9.4) by a biostatistician within sex and 5-year age groups in blocks of ten, and stratification was performed by numbers of treatable legs. For patients who required intervention in bilateral iliac arteries, randomization was performed according to the treated arteries. The sealed, opaque, consecutively numbered envelopes were used to keep the allocation code for each participant, which will be kept unopened by an independent research assistant. The nurse research coordinator in the operating room will prepare the envelopes and inform the surgeon of the allocation results before intervention. Both nurse research coordinators and biostatisticians were not involved in the perioperative management of patients. The outcome assessors and data analysts will be blinded to the interventions.

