### Trial status

Ethics approval has been granted before submission. The trial is currently in the recruitment phase. Study enrollment began on 1 June 2020. It is estimated that recruitment will be completed by 1 June 2022, with a study completion date of 1 June 2024. Any protocol amendments will be updated in the Chinese Clinical Trials Registry.

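### Surgeons who recruit and learn the allocations work with one fixed block size of ten, and the text does not settle whether the operating-room nurse or an outside custodian handles the envelopes before disclosure

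*Protocol article*

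**What the plan says.** All of the allocation procedure is in the Protocol article, Allocation and implementation of interventions.

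- Recruitment: before the procedure, "patients will be enrolled, and informed consent will be obtained from all participants by surgeons".
- Sequence: patients are "randomly allocated at a 1:1 ratio to the CBE stenting group or the CSE stenting group" using SAS, "by a biostatistician within sex and 5-year age groups in blocks of ten", with further stratification by the number of legs to be treated. No other block size is mentioned.
- Custody: the codes are in opaque sealed envelopes in number order, "which will be kept unopened by an independent research assistant".
- Disclosure: "The nurse research coordinator in the operating room will prepare the envelopes and inform the surgeon of the allocation results before intervention".
- Separation and blinding: nurse coordinators and biostatisticians take no part in perioperative care. Outcome assessors and data analysts are blinded; surgeons are not listed.

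Study setting gives one centre. Trial status says "The trial is currently in the recruitment phase", with recruitment planned from 1 June 2020 to 1 June 2022. Protocol amendments allows the sample size to be adjusted on the 12-month revascularization result.

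**The concern.** Two features weaken concealment.

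The first is who handles the envelopes. The assistant keeps them unopened, but the nurse who speaks to the surgeon prepares them. If *prepare* means filling them, upcoming codes are known inside the operating room. If it means fetching or opening the next one, the text describes her role wrongly. Either way the two sentences need reconciling.

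The second is prediction by counting. The recruiters are unblinded, work at one centre and use a single block size with five places per arm. Anyone who keeps a tally within a stratum can do better than chance on the next assignment, and is sometimes certain of it.

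There is a motive to use such knowledge. The Introduction links balloon-expandable stents to calcified and bifurcation lesions and self-expanding stents to tortuous vessels, and the Discussion says device choice currently rests on operator preference. Lesion type is not a stratification factor. Enrolment timed to suit the expected device would shift the risk difference, and blinded outcome assessment does not correct a baseline imbalance.

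**Working it through.** **Inputs from the article.** Block size 10, ratio 1:1, strata of sex by 5-year age group by number of treatable legs, noninferiority margin 10 percentage points. The number of allocations is taken as 106 (lesions in Sample size calculation, patients in the abstract). The plan states no predictability figure, so there is none to reproduce.

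**Assumptions, not in the article.** Mean age 67, SD 7-9, 80-90% male, 30-35% bilateral. The observer sees every earlier allocation in the stratum and always guesses the arm with fewer assignments so far; a tie is a coin toss.

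**Step 1, a filled block of ten (m = 5 per arm).**
- Expected forced assignments: 2m/(m+1) = 10/6 = 1.67 of 10, or 16.7%.
- Chance of a correct guess by position: 0.50, 0.556, 0.556, 0.595, 0.595, 0.643, 0.643, 0.722, 0.722, 1.00; mean 0.653.

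This is a ceiling. It does not describe the trial, because the strata leave most blocks unfinished.

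**Step 2, the stated strata.** With 6 to 10 age bands (assumed) there are 6 x 2 x 2 = 24 to 10 x 2 x 2 = 40 strata, so 106/40 = 2.7 to 106/24 = 4.4 allocations per stratum on average. Simulation of 106 allocations gives:
- assumed age, sex and leg distribution above: 58-60% correct, about 5-7% forced;
- a second skewed set (80/20 by sex, 60/40 by legs, 6-10 age bands): 57-59% correct, 2.7-6.2% forced;
- evenly filled strata: 54-57% correct, 0.1-1.2% forced.

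Across these sets about 0 to 7 or 8 of the 106 assignments would be certain.

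**Step 3, effect on the risk difference.** Suppose the enroller brings one type of patient when expecting one device and another type when expecting the other, and the types differ in risk by D. With guessing accuracy g, the expected type makes up a share g of one arm and 1 - g of the other, so bias = (2g - 1) x D. D is not in the article; take 10 points.
- g = 0.58: 0.16 x 10 = 1.6 points.
- g = 0.60: 0.20 x 10 = 2.0 points.
- g = 0.54 (evenly filled strata): 0.08 x 10 = 0.8 points.

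Bias scales with D: at g = 0.60, D = 5 gives 1.0 point and D = 20 gives 4.0. Every figure supposes that each guess is made from complete records and acted on, so these are upper limits for the given D.

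**Step 4, would varying the blocks help?** Same assumed strata, with a guesser who uses only the running count and does not know the block sizes:

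| Blocks | Correct guesses |
|---|---|
| Fixed 10 | 58-60% |
| Varied 8/10/12 | 58-60% |
| Varied 6/8/10 | 60-62% |
| Varied 4/6 | 64-65% |

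Varying undisclosed sizes removes certainty but not the running-count guess. Small blocks make that guess better.

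**Step 5, does publication matter?** The article is dated 12 May 2022. Planned recruitment runs 730 days from 1 June 2020, and publication falls on day 710, leaving 20 days. Printing the block size adds little by the planned dates, though the team could have known it internally.

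**The case against.** The best defence is that the concealment elements are there: opaque sealed envelopes in number order, a custodian who keeps them unopened, and a nurse and biostatistician with no part in perioperative care. In a condensed article, preparing an envelope in the operating room may only mean getting the next one ready. The fine stratification leaves few assignments certain. The article does not give the number of surgeons or say that anyone tracks results by stratum, so a surgeon who sees every past assignment is an inference. Part of any selection would act through lesion anatomy, which Data collection and management says is measured and which adjusted models could partly address.

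Most of this stands, and it limits the size of the point. It does not settle who fills the envelopes. The nurse's absence from perioperative care does not help either, since the issue is her foreknowledge and her contact with the enroller. Adjustment reaches only features that are measured and put in the model.

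A reader might infer that assignments are known before consent. The text does not support that: consent and enrolment come first, then allocation, then disclosure in the operating room, and the nurse has no stated part in enrolment. A reader might also apply the filled-block accuracy of 65% to the whole trial, or take the full 10 points of an assumed D as the bias. The first ignores the stated strata. The second assumes that all codes leak, which no section says.

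**Conclusion.** The point holds in a limited form. The handling of envelopes is described in two ways that do not fit together, and this is the more important half: if the nurse fills them, upcoming codes sit with the person in contact with the recruiting surgeon. The fixed block size adds a modest weakness: about 58-60% correct guesses and 5-7% forced assignments under the assumed age, sex and leg distribution, less if strata fill evenly. For an assumed 10-point difference between steered patients, that is at most about 1.6-2 points of bias against a 10-point margin. It rests on complete tracking by stratum and on action at every guess, neither of which the article shows. Because enrolment-stage selection cannot be fully repaired in analysis and the correction is cheap, it should be made.

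**What to change.** For all remaining allocations, including any added under the sample size adjustment in Protocol amendments:

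1. State that the biostatistician or the independent research assistant, outside the operating room, fills, seals and holds the envelopes, and releases one only after the patient's consent and trial number are logged.
2. Limit the nurse coordinator to relaying that one allocation, and delete the statement that she prepares the envelopes.
3. Generate unused numbers with varying block sizes centred on ten, for example 8, 10 and 12, and do not disclose them to the clinical team until recruitment ends. Avoid small blocks such as 4 and 6.

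If recruitment has ended, report who in fact filled, held and opened the envelopes.

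The cost is a short amendment and one rerun of the SAS list, with the same staff and envelopes, and slightly looser balance within strata whose last block is unfinished.

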**Methods:**

This trial is a prospective, single-center, parallel, noninferiority, randomized controlled trial. A total of 106 patients will be enrolled and these patients will be randomized to either the CBE stent group or the CSE stent group. The primary end point of the study is the occurrence of target lesion revascularization (TLR) at 12 months after the intervention.

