#### Secondary outcomes

The following secondary endpoints of this study are collected at 1, 6, 12, 24, and 36 months post-index procedure:

(1) Stent and/or surgery related mortality; (2) all-cause mortality; (3) amputation-free survival; (4) acute limb ischemia rate; (5) major adverse cardiovascular and cerebrovascular events (MACCEs); (6) target vessel revascularization (TVR) (TVR is defined as the first revascularization procedure (e.g. PTA, stenting, surgical bypass, etc.) in the target vessel(s)); (7) primary patency (the loss of primary patency is defined as target lesion(s) is determined to be > 50% stenosis or TLR/TLR needed in follow up); (8) primary assisted patency (the loss of primary assisted patency is defined as target lesion(s) is determined to be > 50% stenosis after TLR); (9) secondary patency (the loss of secondary patency is defined as target lesion(s) is determined to be > 50% stenosis after endovascular procedure or surgical bypass TVR); and (10) stent-related complication (e.g., stent kinking or fracture).

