### Sample size calculation

We calculated the sample size for this study based on the results of previous studies [4, 13]. As is reported previously in AIOD patients, the 9-month primary patency of CBE stent (BARD®LIFESTREAM™ Stent) was 89.1%, while the 9-month primary patency of the CSE stent (GORE® VIABAHN™ stent) was estimated to be 82.2% based on VIASTAR Trial [14, 15]. In the present study, we hypothesized that the primary patency of CBE stent is not inferior to that of CSE stent; the predetermined noninferiority margin on risk difference scale (δ) is set as 10% between treatment groups. The type I error rate is 0.05, the power of the test is set as 80%, and the randomization ratio is set as 1:1. After accounting for a 15% dropout rate. It was calculated that 53 lesions per group are needed for a total of 106 lesions.

In order to achieve adequate participant enrollment, we will recruit patients by putting up posters or advertising on the Internet, furthermore, we actively recruit patients from outpatient department and emergency department.

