### Statistical analysis

R studio Version 1.2.1335 (http://www.R-project.org) and Empower (www.empowerstats.com, X&Y solutions, Inc., Boston, MA) were utilized for statistical analysis. Categorical data are expressed as numbers and rates, while continuous data are expressed as means ± standard deviation (SD) if they are normally distributed, or median (interquartile range [IQR]) vice versa. Student’s *t* test or Mann-Whitney *U* test is used for univariate analysis of continuous data, and the *χ*^2^ test or Fisher’s exact test is used for categorical data. For primary analyses, multivariate logistic regression is adopted to calculate adjusted odds ratios (ORs) and 95% confidence interval (95% CI) for short-term outcomes. Cox proportional hazard regression analysis is used to generate adjusted hazard ratio (HR) and corresponding 95% CI for long-term outcomes. The primary and secondary end points will be analyzed in the modified intention-to-treat analysis, which includes all subjects undergo randomization and subsequent interventions. Sensitivity analyses of primary and secondary endpoints are performed in the per-protocol population, based on the treatment actually received. The noninferiority margin was set at 10 percentage points for the absolute difference between groups. If the standard of noninferiority was reached, the primary and secondary outcomes were subsequently tested for superiority (*P*<0.05). Noninferiority will be considered proven if conclusions drawn from the intention-to-treat and per protocol analyses are consistent.

Further pre-specified subgroup analyses will be carried out in the following subgroups: TASC II C-D lesions versus A-B lesions, occlusion versus stenosis. Adjustment analyses for primary and secondary endpoints were performed based on the Hochberg method [16]. Multiple imputation was used to handle missing data.

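### The target of 106 is given both as patients and as lesions, and the rule for bilateral patients leaves open whether the patient or the artery is randomised; no method is named for two legs per patient

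*Protocol article*

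**What the plan says.** All places are in the protocol article.

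- **Abstract, Methods:** "A total of 106 patients will be enrolled and these patients will be randomized". The unit is the patient.
- **Sample size calculation:** "53 lesions per group are needed for a total of 106 lesions". The unit is the lesion, and the number is the same.
- **Allocation and implementation of interventions:** it begins with patients, "The included patients were randomly allocated at a 1:1 ratio to the CBE stenting group or the CSE stenting group". The list is drawn up "within sex and 5-year age groups in blocks of ten, and stratification was performed by numbers of treatable legs", and the number of legs is a property of the patient. The envelopes hold one code per participant. For bilateral disease, however, "For patients who required intervention in bilateral iliac arteries, randomization was performed according to the treated arteries".
- **Primary outcome:** target lesion revascularization (TLR) at 12 months, defined on the target lesion or lesions.
- **Secondary outcomes:** some belong to the lesion (patency) and some to the patient, for instance "all-cause mortality; (3) amputation-free survival" and major adverse cardiovascular and cerebrovascular events (MACCE).
- **Statistical analysis:** logistic regression for short-term and Cox regression for long-term outcomes, in a modified intention-to-treat set "which includes all subjects undergo randomization and subsequent interventions". No pairing, clustering, robust variance or random effect is named.

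**The concern.** The target cannot be 106 in both units once some patients have two treated legs, so the article does not fix when recruitment is complete.

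The bilateral sentence then has two readings, and each has its own cost:

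- **Both legs share one allocation.** Two lesions of one patient sit in the same arm and are likely to be positively correlated. A lesion-level model that treats them as independent gives intervals that are too narrow. In a noninferiority trial this works towards a false claim of noninferiority.
- **Each artery has its own allocation.** One patient can carry both stent types. The lesion outcomes still have an arm, but a death, a MACCE or an amputation in that patient does not.

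A later analysis plan could supply a clustered model. It could not give an arm to a patient who has already received both stents, and it could not settle which unit the stated target refers to.

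**Working it through.** **Inputs from the Sample size calculation section.** Primary patency 89.1% with the balloon-expandable stent (CBE) and 82.2% with the self-expanding stent (CSE), margin 10 percentage points, type I error 0.05, power 80%, 1:1, dropout 15%. Whether the type I error is one-sided is not stated.

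**Assumptions, because the article gives neither figure.** Share of bilateral patients f = 0.2 to 0.5, with one lesion per treated side; within-patient correlation ICC = 0.3 to 0.5.

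**Step 1. The plan's own figure.**
- Variance term: 0.822 × 0.178 + 0.891 × 0.109 = 0.2434.
- Distance to the margin: 0.10 + 0.891 − 0.822 = 0.169.
- At one-sided 0.05, n = 0.2434 × (1.645 + 0.842)² / 0.169² = 52.7, so 53 per group.

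This matches the stated 53, but as the number before dropout. The formula treats lesions as independent. Power at 53 per group is 80.2%.

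**Step 2. Patients against lesions.** Lesions = patients × (1 + f).

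| f | patients who supply 106 lesions | lesions from 106 patients |
|---|---|---|
| 0.2 | 106 / 1.2 = 88 | 127 |
| 0.5 | 106 / 1.5 = 71 | 159 |

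**Step 3. Both legs in the same arm.** Design effect DE = 1 + ICC × 2f / (1 + f). The correct standard error (SE) is √DE times the naive one. Power = Φ(0.169 / √(0.2434 × DE / 53) − 1.645).

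| f | ICC | DE | correct SE / naive SE | effective lesions per arm | power before dropout |
|---|---|---|---|---|---|
| – | 0 | 1.00 | 1.00 | 53 | 80% |
| 0.2 | 0.3 | 1.10 | 1.05 | 48 | 77% |
| 0.5 | 0.5 | 1.33 | 1.15 | 40 | 70% |

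If the naive standard error is used all the same, the true one-sided error at the margin is 1 − Φ(1.645 / √DE). That is 5.8% at DE 1.10 and 7.7% at DE 1.33, instead of 5%.

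**Step 4. Each artery allocated independently.** Pairs in the same arm and pairs in opposite arms roughly cancel. In a simulation of 106 lesions with about 14% events, the true and naive standard errors were 0.0674 and 0.0671 (f = 0.2, ICC = 0.3) and 0.0677 and 0.0670 (f = 0.5, ICC = 0.5), a gap of about 1% or less. With independent 1:1 draws, about half of bilateral patients carry both stents, which is 10-25% of all patients. For 106 lesions this is about 9 of 88 patients (88.3 × 0.2 / 2) to 18 of 71 (70.7 × 0.5 / 2).

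**Step 5. Legs always split between arms.** The factor becomes 1 − ICC × 2f / (1 + f), which is 0.90 to 0.67. Ignoring the pairing is then conservative.

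**The case against.** **Split patients are not proven.** The allocation section randomises patients, stratifies by a patient-level factor and keeps one code per participant. All of this points to one allocation per patient. This stands: a reader might infer that bilateral patients were in fact put in both arms, but the text only leaves that possible. It does not remove the contradiction with the sentence on treated arteries.

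**The two harms exclude each other.** The loss of precision needs both legs in the same arm; the patient-level problem needs them in different arms. This also stands, so no unconditional statement that the standard errors are wrong or the trial underpowered can be made from this point.

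**Part of any power shortfall has another cause.** With 15% dropout, 53 lesions leave about 45 per arm, and power is 74% even if all lesions are independent. That fall from 80% belongs to the dropout allowance, not to clustering, and is kept out of the figures here.

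**A condensed article may leave clustering to the analysis plan.** Fair. All that can be said is that the statistical analysis section names no such method. The conflict between 106 patients and 106 lesions, however, is stated in the article itself.

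**The strata and blocks.** A reader might infer that sex, 5-year age and leg strata in blocks of ten spoil the balance. The article gives no age range beyond 18 years and over, so the number of strata is unknown. The effect would be small in any case: a split of 48 to 58 raises the variance by 0.9% ((1/48 + 1/58) / (2/53) = 1.009). This is no part of the point.

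**Conclusion.** The unit conflict holds on the article's own words and needs no assumption: 106 patients and 106 lesions cannot both be the target when some patients have two treated arteries. The bilateral sentence and the one-code-per-participant procedure must be reconciled.

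The size of the consequence is conditional. With both legs in one arm, 20-50% bilateral patients and a correlation of 0.3-0.5, the correct standard error is 5-15% larger than the naive one and power with 53 lesions per arm is 77-70% instead of 80% before dropout. With independent allocation of arteries, precision is nearly unchanged, and the damage is to death, MACCE and amputation-free survival in patients who carry both stents. Which of the two applies cannot be read from the article.

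**What to change.** 1. State one unit of randomisation, give the target in that unit, and give the matching numbers of patients and lesions.
2. State whether the two arteries of a bilateral patient share one allocation. For any patient still to be randomised, use one allocation per patient.
3. Analyse lesion-level outcomes (TLR, patency) with patient-clustered standard errors, by GEE or a robust variance. This is valid whichever way the legs were allocated.
4. In patient-level comparisons, report patients carrying both stents separately, with a sensitivity analysis of how they are handled.

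Cost: mainly wording and a standard model option. Confidence intervals may become slightly wider, and patient-level comparisons lose any patients with both stents. The change to allocation can reach few patients, because the trial status section expects recruitment to end by 1 June 2022 and the article appeared on 12 May 2022. The gain lies mostly in items 1, 3 and 4 and in documenting how past bilateral patients were allocated.

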### Details of intervention

The included patients will receive the same perioperative management, including antiplatelet drugs, statin usage, and blood controls. Both common femoral arteries and sometimes brachial artery will be used for access. Whether to adopt percutaneous or cutdown access route will be determined by the surgeons. After obtaining arterial access, 0.5 mg/kg of unfractionated heparin will be administered. A fluor opaque ruler will be used to record the location and extent of the lesion. Both intraluminal and subintimal recanalization of iliac lesions will be allowed. After the successful passage of the guidewire, the target lesion will be predilated with downsized balloon in CBE group, and with equal-sized balloon in CSE group. During actual intervention, the allocated choice of covered stents may be modified according to intraoperative findings, for instance, the length of lesions did not match the stents. Multiple stents are required when needed and multiple stent edges should overlap by at least 10 mm. Furthermore, additional bare metal stents can be added in both groups, according the discretion of surgeons. Post-dilation balloon will be performed within the stented segment, with less than 10% oversizing. Final angiography will be performed after the intervention in both groups, with the same angles and magnifications as the baseline angiography.

Postoperative management include a dual antiplatelet regimen for 3 months, involving 100 mg of aspirin once a day plus 75 mg of clopidogrel once a day. Clopidogrel is not required if a participant is taking warfarin; other direct thrombin inhibitors, factor Xa inhibitors, or low molecular weight heparin will be used according to the physician’s recommendation. Anticoagulant therapy will be discontinued when other surgical procedures are needed, and then, the participant will resume anticoagulant therapy as soon as possible after the surgery. Drug side effects will be checked and monitored at outpatient visit or telephone follow-up. According to the comprehensive surgeon’s recommendation, drug therapy will be discontinued. Clinical follow-up will be planned at 1, 6, 12, 24, and 36 months to evaluate clinical outcomes.

